### Schedule of events and procedures

**Table 2. T2:** Schedule of visits and procedures. Visit 1 may occur up to four weeks before visit 2. X: event scheduled to occur throughout the study. A: event scheduled to occur only in Phase A. B: event scheduled to occur only in Phase B. *: Timeline is approximate only, as exact timings (± time windows) of visits relate to the actual (not intended) date of the previous visit. **in a selected subset of participants only. Phase A: punch biopsy is the gold standard comparator for BCG recovery
^
15
^ but is invasive, requiring local anaesthetic and a suture to close the wound. Our aim will be to validate less invasive techniques including minimally invasive skin biopsy
^
17
^ and a skin scrape
^
18
^ in the pilot phase (n=10) of the study. Phase B (n=20): we will select the optimal minimally invasive skin technique(s) from phase A and apply these longitudinally during study visits to assess BCG growth kinetics and interrogate immune responses over time. No local anaesthetic (LA) is required for minimally invasive biopsy; LA is known to cause artefactual blunting of humoral immune responses in laboratory assays. Nasal and throat swabs will be used to exclude SARS-CoV-2 infection prior to BCG challenge on day 0 (rapid antigen test) and subsequently to check for co-existent respiratory viral infection using PCR techniques. $ If screen >7 days from BCG. Β If virtual chat. Total blood volume per visit 50ml.

Study visit		1	2	3	4	5	6	7
Study day	Initial consent	Screening	Day 0	Day 2	Day 7	Day 14	Day 21	Day 28
Time windows (days) *				±1	±2	±2	±2	±5
Consent (Written)	x	xβ						
Consent (Verbal)	x	x	x	x	x	x	x	x
Eligibility check	x							
History and examination		x						
Vital Signs		x	x	x	x	x	x	x
Urine β-HCG		x	X$					
Screen for AEs			x	x	x	x	x	x
BCG challenge injection			x					
Skin punch biopsy						X		
Skin micro biopsy ^ 17 ^			B	B	B	x		
Skin scrape ^ 18 ^						A		
Skin swab			x	x	x	x	x	x
Inspect + photograph site			x	x	x	x	x	x
Stitch removal							X	
Diary card provided			x					
Diary card collected								x
FBC		x						
Coagulation		x						
PBMCs		x		x	x	x		
Serum			x	x	x	x		
HIV serology		x						
Blood RNA			x	x	x	x		
Nasosorption			B	B	B	B	B	B
Nasal wash **			B	B	B	B	B	B
Nasal scrape			B	B	B	B	B	B
Nasal & throat swab		B	B	B	B	B	B	B

**Table 3. T3:** Clinical assessment and STOP criteria.

Clinical history and examination	STOP if unexplained or concerning findings on history or examination

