### Study design

Prospective longitudinal controlled human infection study after intradermal injection with BCG SSI in two phases: Phase A is designed to confirm microbiological recovery and determine agreement between the current gold standard of skin punch biopsy 14 days after injection with minimally invasive biopsy techniques. Phase B is designed to refine and optimise immunological assays to measure local (using optimal minimally invasive techniques), systemic (blood) and respiratory mucosal responses to intradermal BCG injection.

**
Phase A
**

Ten participants will receive a single intradermal injection to the upper arm of BCG SSI 6–24 × 10
^5^ colony forming units in line with an optimised and established existing protocol
^
15
^. The BCG SSI strain has been chosen as the UK licensed vaccine for TB. The dose (3x higher than that used in routine vaccination) has been chosen based on study findings by Minhinnick
*et al.*
^
15
^, who demonstrated good mycobacterial recovery at this concentration with no increase in participant adverse events between the doses. Participants will be followed up longitudinally with active assessment for tolerability; adverse events; and serious adverse events. We will determine BCG SSI recovery from the intradermal injection site 14 days later by classical microbiology and molecular diagnostic techniques using gold standard punch biopsy
^
15
^ as our primary outcome measure. In parallel, and after local anaesthetic injection, we will obtain paired minimally invasive samples (skin swab, skin scrape
^
18
^ and microbiopsy
^
17
^ from the same skin site at 14 days and determine agreement of BCG SSI recovery by classical microbiology and molecular diagnostic techniques with punch biopsy

Parameters for progression from Phase A to Phase B are:

1.Participants able to tolerate study procedures2.No experimental challenge related SAE or SUSAR detected3.Confirmation of BCG recovery by classical microbiology or molecular techniques from punch biopsy at day 14 in all 10 participants who received intradermal BCG challenge4.Confirmation of BCG recovery by classical microbiology or molecular techniques from any of the minimally invasive skin sample technique (swab, scrape and microbiopsy) at day 14 in ≥9 participants who received intradermal BCG challenge.

**
Phase B
**

Twenty participants will receive a single intradermal injection to the upper arm of BCG SSI 6–24 × 10

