**Symptom diary:** We will request that participants complete a symptoms diary for 14 days after intradermal injection. Participants will be asked to grade any symptoms from 0–4 on a Likert scale. This format has been previously utilised in our experimental human pneumococcal carriage studies. The results will be reviewed at visits D2 and D7. Participants will be advised to ensure the clinical team are contacted with any moderate to severe symptoms as soon as possible. Further details on clinical symptom scores and how these will be assessed are described in a specific section below.

**
Challenge visit (B)
**

*

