https://www.nanopass.com/). After intradermal injection, participants will stay in the unit for 15 minutes and have a clinical review at this point. During the administration of the challenge agent, resuscitation medicines and equipment will be immediately available for the management of anaphylaxis.

**
Safety procedures
**

Written and verbal instructions are given to the participant describing potential mild, moderate and severe symptoms and the instances to consult the study team.

Participants will be instructed to monitor the development of any symptoms and report them to the clinical team immediately. Home monitoring of symptoms will include a clear flow chart of the necessary intervention should any symptoms develop (see participant safety information sheet).

**
Confirmation and quantification of mycobacterial recovery
**

Skin biopsy specimens will be cryopreserved and subsequently processed in batch. Typically, each biopsy specimen will be thawed in a 37°C water bath and transferred to an appropriate tissue homogenising platform
^
16
^. A total of 100 μL of neat homogenate and 100 μL of a 10
^-1^ dilution, in sterile PBS, will be plated in triplicate onto Middlebrook 7H11 agar. The BCG SSI vaccine vials will be reconstituted in PBS, and 100 μL of appropriate dilutions will be plated in triplicate as positive controls. Plates will incubated at 37°C for 4 weeks before counting. The remaining biopsy specimen homogenate will be stored at −80° for subsequent DNA extraction.

**
DNA extraction
**

Biopsy specimen homogenate will be thawed, and BCG DNA from 200 μL of homogenate will be released using standard methods. Typically, a tough microorganism (bead beating) lysing kit will be used. Homogenate will be transferred to a separate tube and 50 μL PBS used to wash remaining homogenate from the beads. A total of 180 μL of ATL buffer and 20 μL of proteinase K (Qiagen) will be added, and the homogenate vortexed and incubated at 56°C for 4 hours. Following this step, extractions will be performed as previously described
^
16
^.

**
Quantitative polymerase chain reaction
**

Appropriate primers be used for detection of BCG DNA. These are optimised modifications
^
16
^ of an early template complementary to regions flanking the BCG deletion sequence, RD1, and amplify a 196–base pair fragment
^
22
^. Polymerase chain reaction (PCR) analyses will be performed as previously described
^
16

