•   Similar pattern of response to that seen to BCG intradermal injection, or

3 = Definite

•   Reasonable temporal relationship to BCG intradermal injection and

•   Event not readily produced by alternative aetiology (clinical, environment, or other interventions), and

•   Known pattern of response to BCG intradermal injection.

The chief investigator (CI), with the consultation of the trial steering committee (TSC), if required, will determine causality of AEs. The greatest degree of causal relationship (definite > probable > possible > unlikely related > not related) determined by either the PI or TSC after their discussions will determine the ultimate classification of the AE. Definite (4), probable (3) and possible (2) are considered to be related. No relationship (0) and unlikely (1) are unrelated.

**Table 5. T5:** Expected adverse events.

Expected adverse events
Pain/tenderness at the injection or biopsy site
Redness at the injection or biopsy site
Swelling at the injection or biopsy site
Warmth at the injection or biopsy site
Scaling/pustules at the injection or biopsy site
Transient ipsilateral axillary lymphadenopathy <1cm diameter
Scar at challenge (and biopsy site)
Headache
Fever (>38.3°C)

**
Procedure for recording adverse events
**

Participants will be asked to complete diary cards for 14 days after BCG challenge. They will be provided with a thermometer and tape measure to enable daily recording of temperature and local reactions at the injection site.

The diary cards will be reviewed at follow up visits and adverse events recorded in the CRF. Outside the diary card periods, expected local and systemic AEs (listed in
Table 5) will be specifically asked about and graded by severity (as detailed in
Table 6). Participants will be given the opportunity to report any other new symptoms since the last visit with start and stop dates and any treatments undergone.

All AEs (whether reported by the volunteer or solicited by the Investigator) will be clinically assessed at each visit and recorded in the CRF.

The following information will be recorded: description, date of onset and end date, severity and any treatment or intervention undertaken. The severity of events will be assessed on the following scale: 1 = mild, 2 = moderate, 3 = severe.

An assessment of relatedness to the BCG challenge will then be made by the Investigator.

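### The 14-day symptom diary stops on the nominal day of the punch biopsy, so reactions after it have no planned daily record

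*Protocol article*

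**What the plan says.** The diary length is stated twice. The symptom diary paragraph under Description of study interventions and study procedures says "We will request that participants complete a symptoms diary for 14 days after intradermal injection". Safety reporting (Procedure for recording adverse events) gives the same 14 days from challenge and supplies a thermometer and tape measure "to enable daily recording of temperature and local reactions at the injection site".

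Table 2 and Study design put the punch biopsy on Day 14. In Phase A the swab, scrape and microbiopsy are taken "from the same skin site at 14 days". The punch needs local anaesthetic and one or two sutures. The clinical samples list plans it for 10 participants in Phase A and 20 in Phase B, although the Phase B description speaks of replacing it with less invasive sampling. Phase B microbiopsies are at D0, D2, D7 and D14.

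After the diary, Safety reporting provides for visit-based capture: "Outside the diary card periods, expected local and systemic AEs" listed in Table 5 are solicited and graded. It also says "The diary cards will be reviewed at follow up visits and adverse events recorded in the CRF". Table 2 schedules "Inspect + photograph site" at Day 21 and Day 28, and the safety procedures add: "Participants will be instructed to monitor the development of any symptoms and report them to the clinical team immediately".

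Tables 5 and 6 cover pain, redness and swelling at the injection site or the biopsy site. Table 6 grades redness and swelling in millimetres.

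**The concern.** The diary length is tied to the injection, whereas the secondary safety objective and the first progression criterion concern the study procedures as a whole. The procedure most likely to test tolerability falls where the daily record stops, and nothing in the article restarts or extends it.

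The evidence before and after the biopsy therefore differs in kind. Before it, the highest daily grade is available. After it, grades come from inspection and questioning at a visit some days later, or from what a participant chose to report. Redness or swelling that has already gone cannot be measured at that visit, so the grade after the biopsy could be understated relative to the grade before it. The study also hypothesises that minimally invasive sampling will be more acceptable than the punch, which makes the period after the punch worth recording well.

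**Working it through.** No sample size or power figure is involved; the check is day arithmetic.

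**Inputs**
- Last diary day: 14 (symptom diary paragraph; Safety reporting).
- Nominal biopsy day: 14. Nominal next visit: Day 21 (Table 2).
- Windows: Day 2 ±1, Day 7 ±2, Day 14 ±2, Day 21 ±2. The Table 2 footnote says "visits relate to the actual (not intended) date of the previous visit", so the windows accumulate.

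**Nominal days**
- Full diary days after the biopsy: 14 − 14 = 0.
- Full days between the biopsy and the Day 21 visit: 21 − 14 − 1 = 6, none with a daily record.

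**Simple ±2 window around Day 14**
- Biopsy on day 12 to 16, so the diary covers 14 − 12 = 2 days after it at most, and 0 at least.

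**Chained windows**
- Day 2 visit: day 1 to 3.
- Day 7 visit: previous visit + 3 to 7 days.
- Day 14 visit: previous visit + 5 to 9 days, so day 9 to 19.
- Day 21 visit: previous visit + 5 to 9 days, so day 14 to 28.
- Combinations: 3 × 5 × 5 × 5 = 375.

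Let B be the biopsy day and g the gap to the Day 21 visit (5 to 9 days). Then:
- full days between biopsy and visit = g − 1, from 4 to 8;
- days covered = min(max(14 − B, 0), g − 1);
- days uncovered = (g − 1) − days covered.

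Of the 75 combinations that determine B, the biopsy falls 5, 4, 3, 2 or 1 days early in 1, 3, 6, 9 and 12 (31 in all), and on Day 14 or later in 44. Each pairs with 5 values of g.

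| Quantity | Range | Result with all 375 weighted equally |
|---|---|---|
| Full post-biopsy days covered | 0 to 5 | mean 324/375 = 0.864; none in 44 × 5 = 220 (58.7%) |
| Days uncovered before the Day 21 visit | 0 to 8 | mean 6 − 0.864 = 5.136; none in 5 (1.3%) |

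The total of 324 is 5 × (5·1 + 4·3 + 3·6 + 2·9 + 1·12) = 5 × 65 = 325, less 1 for the single combination where the cap g − 1 = 4 applies to a biopsy 5 days early.

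If an entry made on the biopsy day itself is counted, the combinations with no entry on or after the biopsy are those with the biopsy later than Day 14: 31 × 5 = 155 (41%).

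**The case against.** The best defence is that this is a deliberate two-mode design. The diary is anchored to the challenge, which is also what causality is assessed against. Afterwards, solicited grading takes over, using a list that names the biopsy site. Staff see the wound at Day 21, when the stitch is removed, and again at Day 28. Onset and end dates are recorded for adverse events. Both active and passive collection continue, so the safety endpoint is met as worded, and the progression criterion sets no millimetre threshold. Participants keep the tape measure, so a reaction reported promptly can be measured, and pain can be graded from recall. The diary card and participant safety sheet are not shown. Equal weighting of window combinations has no basis in the documents.

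Most of this stands and limits the point. Follow-up is not absent, and the percentages describe a calendar, not lost safety data. Phase B microbiopsies on D0, D2 and D7 fall inside the diary, so only the Day 14 procedures are affected.

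It does not close the gap. A visit 5 to 9 days after the biopsy cannot recover the peak size of a reaction that has settled, and spontaneous reports are not scheduled measurements. Collecting the card at Day 28 does not lengthen recording, because both statements of duration say 14 days.

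**Conclusion.** The point holds as a minor weakness in a stated design choice. On nominal days the diary gives no full day of recording after the biopsy and leaves the 6 days before the Day 21 visit without a daily record. Under the chained windows, 0 to 5 days are covered and 0 to 8 are not.

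The averages (0.9 days covered, 5.1 uncovered) and the 59% and 1.3% rest on equal weighting of the window combinations, which is an assumption; the 59% also counts full days only and excludes the biopsy day. The ranges do not depend on the weighting.

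The documents give no time course for biopsy reactions, so the number missed cannot be estimated. The safety endpoint and the progression criterion remain usable, but the tolerability evidence is weaker after the biopsy than before it. The gap applies to all 10 Phase A participants. In Phase B it concerns the Day 14 microbiopsy and, where it is done, the punch.

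**What to change.** Continue the diary to the actual Day 21 visit, with daily pain, redness and swelling recorded at the combined injection and biopsy site once the biopsy has been done. Report maximum grades separately for the periods before and after the biopsy. Do not attribute post-biopsy grades to individual procedures: the Phase A samples come from one site on one day, and their reactions cannot be told apart. Merely stating that post-biopsy grades are visit-based would be accurate but would not supply the missing measurements.

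The cost is about 21 − 14 = 7 more entries per participant (0 to 14 under the chained windows). That is nominally 7 × 10 = 70 entries in Phase A and up to 7 × 20 = 140 in Phase B if all 20 have the punch biopsy. No extra visit or equipment is needed: participants already have the tape measure, and the card is collected at Day 28.

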**Preparation and administration of mycobacteria**
*

*Formulation and supply*

BCG SSI contains live attenuated Danish strain 1331
*Mycobacterium bovis* BCG. It is supplied as a powder and solvent for suspension. One vial of SSI reconstituted in 1mL contains 10 doses of 2–8 × 10
^5^ CFU (see SmPC). BCG SSI will be supplied to the Accelerator Research Clinic by the Liverpool University Hospitals NHS Foundation Trust who stock the vaccine for clinical use. All movements of the study challenge agents will be documented. Challenge agent accountability, storage, shipment and handling will be in accordance with local SOPs. Drug movement will occur in a refrigerated container to ensure a cold chain of +2 to +8°C.

*Storage*

Dispensed BCG SSI vials are supplied in boxes containing multiple vials and each vial is clearly labelled with the market product (BCG SSI). All challenge agents to be administered will be stored in a safe and locked place with no access by unauthorised personnel. The BCG will be stored between +2
^o^C and +8°C in a locked fridge. The storage conditions will be under the responsibility of the clinical site. Any temperature deviation outside the range +2 to 8°C will be reported to the CI as soon as detected. Following an exposure to such a temperature deviation, challenge agents will not be used until CI approval has been given.

*Administration*

The correct volume will be drawn up and administered intradermally over the deltoid region of the non-dominant upper arm, according to the site-specific SOP. One vial of SSI reconstituted in 1mL contains 10 doses of 2 – 8 × 10
^5^ CFU (*taken as 5×10
^5^ CFU for this calculation). To achieve the specified dose of 6 – 24 × 10
^5^ CFU we plan to reconstitute in 0.4ml (3 doses 0.1ml doses for administration and an additional dose for post hoc checking of dose administered) This volume will be checked in the laboratory prior to study commencement and may be subject to change in order to achieve the target concentration. We will review the administration concentrations after phase A and may adjust reconstitution volumes to refine the BCG dose in Phase B. Intradermal injection will be standardised in the study by using the FDA marked 0.6mm MicronJet microneedle (
https://www.nanopass.com/). After intradermal injection, participants will stay in the unit for 15 minutes and have a clinical review at this point. During the administration of the challenge agent, resuscitation medicines and equipment will be immediately available for the management of anaphylaxis.

**
Safety procedures
**

Written and verbal instructions are given to the participant describing potential mild, moderate and severe symptoms and the instances to consult the study team.

Participants will be instructed to monitor the development of any symptoms and report them to the clinical team immediately. Home monitoring of symptoms will include a clear flow chart of the necessary intervention should any symptoms develop (see participant safety information sheet).

**
Confirmation and quantification of mycobacterial recovery
**

Skin biopsy specimens will be cryopreserved and subsequently processed in batch. Typically, each biopsy specimen will be thawed in a 37°C water bath and transferred to an appropriate tissue homogenising platform
^
16
^. A total of 100 μL of neat homogenate and 100 μL of a 10
^-1^ dilution, in sterile PBS, will be plated in triplicate onto Middlebrook 7H11 agar. The BCG SSI vaccine vials will be reconstituted in PBS, and 100 μL of appropriate dilutions will be plated in triplicate as positive controls. Plates will incubated at 37°C for 4 weeks before counting. The remaining biopsy specimen homogenate will be stored at −80° for subsequent DNA extraction.

**
DNA extraction
**

Biopsy specimen homogenate will be thawed, and BCG DNA from 200 μL of homogenate will be released using standard methods. Typically, a tough microorganism (bead beating) lysing kit will be used. Homogenate will be transferred to a separate tube and 50 μL PBS used to wash remaining homogenate from the beads. A total of 180 μL of ATL buffer and 20 μL of proteinase K (Qiagen) will be added, and the homogenate vortexed and incubated at 56°C for 4 hours. Following this step, extractions will be performed as previously described
^
16
^.

**
Quantitative polymerase chain reaction
**

Appropriate primers be used for detection of BCG DNA. These are optimised modifications
^
16
^ of an early template complementary to regions flanking the BCG deletion sequence, RD1, and amplify a 196–base pair fragment
^
22
^. Polymerase chain reaction (PCR) analyses will be performed as previously described
^
16
^. A standard curve will be obtained by extracting BCG DNA from 1:10 serial dilutions of 3 pooled BCG Bulgaria vaccine vials in PBS and correcting for live BCG from the corresponding CFU counts on solid agar.

**
Antibody measurement
**

Samples of serum and nasosorption will be retained for antibody measurement using standard ELISA assays.

**
Cellular responses
**

Ex Vivo Interferon γ (IFN-γ) Enzyme-Linked Immunospot (ELISpot) assays will be performed on freshly isolated PBMCs from all participants as documented in
Table 1. Responses to purified protein derivative (PPD) from M. tuberculosis will also be assessed. Unstimulated PBMCs will be used as a measure of background IFN-γ production. Results will be reported as spot-forming cells per million PBMCs, calculated by subtracting the mean count of the unstimulated PBMCs from the mean count of triplicate antigen wells and correcting for number of PBMCs in the well.

**
Genetic responses
**

Samples will be retained for transcriptomic signature feasibility testing. These methods will be essential as the CHIM develops for vaccine testing.

**
Baseline and subsequent clinical assessments
**

Described in
Table 1.

**
Subsequent visits
**

Described in
Table 1.

**
Sample handling
**

Described section 9.6.

**
Early discontinuation/withdrawal of participants
**

If a participant withdraws from the study for any reason, another participant will be recruited to replace them.

**
End of study
**

The clinical phase of the study has ended when the last participant completes their last visit. Recruitment and follow up of participants from initial recruitment activities until last participant finishes their last study visit are planned to be completed within 13 months. The end-of-study is completed when the last laboratory assay is analysed on the last participant sample. At this point all samples will be archived unless transferred to the tissue bank with participant consent for future use.

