^. Candidate vaccines which have passed successfully through phase I trials and are in Phase 2b efficacy studies could be included in a TB CHIM, which could be designed to either measure prevention of infection (POI) or immunological endpoints. This would allow vaccine discovery to accelerate in a cost-effective manner. Similarly, a responsive TB CHIM could accelerate the development of new drugs and promote refinement of drug combination regimens.

There are current concerns in using wild type
*M.tb* as a human challenge agent given that infection cannot be reliably eradicated, treatment is prolonged with toxicities and there is a risk of relapse or recurrent infection
^
11
^. BCG contains live attenuated
*Mycobacterium bovis* which forms part of the
*Mycobacterium tuberculosis* complex and is replication competent but does not usually cause clinical TB disease in immunocompetent individuals. A recent systematic review and workshop discussion of TB CHIM in the UK and Malawi identified several CHIMs using BCG
^
11
^. Intradermal injection with BCG was associated with expected side effects following routine vaccination with no serious adverse events (SAEs) reported in any of the identified studies. Disseminated BCG-disease has been reported in infants after routine intradermal vaccination and after intravesical installation (as chemotherapy to prevent recurrences of carcinoma in situ and/or Ta/T1 papillary tumours of the bladder) but this is extremely uncommon, primarily affecting immunocompromised individuals and readily treatable using standard anti-tuberculosis therapy
^
12
^. The workshop discussion agreed that BCG was currently the preferred agent to optimise a TB CHIM as it is licensed worldwide, has a long-established safety profile, is usually selected as the control agent in novel vaccine studies, and has been reliably recovered from previous challenge models with optimised dosing.

We are working in collaboration with partners at the University of Oxford who have established a CHIM using intradermal BCG and have published several peer reviewed articles
^
13–
16
^. They found optimal BCG recovery with punch biopsies at 2 weeks post intradermal BCG injection and using three times the standard BCG dose, without additional adverse events
^
15

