## Discussion

The establishment of a safe and effective CHIM for Tuberculosis would accelerate much needed vaccine and therapeutic development. A skin challenge model allows straightforward and reliable isolation of BCG, the key outcome measure of a TB human challenge model. Furthermore, participant procedures are safe and well tolerated and BCG has a long-established safety profile. For this reason, an intradermal BCG challenge model remains the most feasible TB CHIM currently and continued development and refinement of protocols remain important
^
11
^.

A previously conducted BCG intradermal model found optimal BCG recovery when using three times the dose of the UK licensed BCG SSI
^
15
^. This model reliably isolated BCG by culture and PCR from punch biopsies and detected a vaccine effect of prior BCG
^
13
^. We therefore aim to replicate and further refine this model. Given punch biopsy is an invasive procedure, serial sampling with this technique in individual participants is not feasible. Our study is designed to compare BCG isolation for different minimally invasive skin sampling techniques, that may then be used for serial monitoring of mycobacterial recovery and of the compartmental immune response over time, optimising end points of the challenge model for use in vaccine evaluation. 

A recently conducted systematic review and workshop in Liverpool and Malawi highlighted the limitations of an intradermal BCG CHIM and the extent to which it can be used to model M.tb infection in TB vaccine evaluation
^
11
^. Firstly, the immune response to WT-M.tb is complex and can lead to a wide range of disease manifestations after initial primary infection. Furthermore, the immune response to BCG is highly variable according to age, geography and prior non-tuberculous Mycobacterium exposure and the correlates of protection are not fully known. Finally, the compartmental skin response to intradermal BCG will likely differ to pulmonary M.tb given the variation in immune populations at these sites. However, one study has shown concordance between the transcriptional profile of skin punch biopsy specimens from TST injection sites with human pulmonary granulomas suggesting correlation between the compartmental skin and pulmonary immune response to
*M.tb
^
22
^
*.

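### Reconstituting a vial in 0.4 mL and injecting 0.1 mL gives 5–20 × 10^5 CFU (2.5 times the routine dose), not the specified 6–24 × 10^5 CFU (3 times)

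*Protocol article*

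**What the plan says.** The Protocol article fixes the challenge dose in Study design, Phase A: each participant receives a "single intradermal injection to the upper arm of BCG SSI 6–24 × 10"^5 CFU (the exponent follows in the text). Phase B repeats the same range. The multiple is given in the Phase A text: "The dose (3x higher than that used in routine vaccination". The reason for that multiple is earlier work with this model. The Introduction reports best recovery "using three times the standard BCG dose, without additional adverse events", and the Discussion says a previous model "found optimal BCG recovery when using three times the dose of the UK licensed BCG SSI".

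The preparation is described under Preparation and administration of mycobacteria. The vial content is given as "One vial of SSI reconstituted in 1mL contains 10 doses of 2–8 × 10"^5 CFU, and 5 × 10^5 CFU per dose is adopted for the calculation. To reach the specified range, the Administration text then says "we plan to reconstitute in 0.4ml (3 doses 0.1ml doses for administration and an additional dose for post hoc checking of dose administered". It adds "This volume will be checked in the laboratory prior to study commencement", that the volume may change to reach the target concentration, and that concentrations will be reviewed after Phase A and may be adjusted for Phase B.

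**The concern.** The inputs, the preparation and the target dose are all printed together, and the preparation does not produce the target. The range 6–24 × 10^5 is exactly three times 2–8 × 10^5. Splitting one vial into four equal portions gives each portion ten quarters, or 2.5, of a routine dose.

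The multiple matters because it is the only justification the protocol offers for the dose, and the study sets out to replicate a model run at three times routine. The primary endpoint is the quantity of BCG recovered at day 14 (Table 1). Progression to Phase B requires recovery from punch biopsy in all ten Phase A participants. Both rest on the dose actually given. In addition, vials near the bottom of the label range would deliver less than the protocol's own minimum.

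**Working it through.** **Inputs, all from the Protocol article**

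- Vial content: 10 routine doses of 2–8 × 10^5 CFU, nominally 5 × 10^5 each (Formulation and supply; Administration).
- Planned reconstitution volume 0.4 mL and injection volume 0.1 mL; three injections and one check dose per vial (Administration).
- Target: 6–24 × 10^5 CFU in a single injection, three times routine (Study design, Phase A).

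**Step 1. Reproduce the target.** 3 × (2–8 × 10^5) = 6–24 × 10^5 CFU; nominal 3 × 5 × 10^5 = 15 × 10^5 CFU. The nominal 15 × 10^5 is not printed in the protocol; it follows from the stated multiple and the stated nominal dose.

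**Step 2. Dose from the planned preparation.** CFU per injection = (10 × CFU per routine dose) × injection volume / reconstitution volume. With 0.1/0.4 = 0.25:

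| CFU per routine dose (×10^5) | Vial (×10^5) | 0.1 mL of 0.4 mL (×10^5) | Three times routine (×10^5) |
|---|---|---|---|
| 2 (low) | 20 | 5 | 6 |
| 5 (nominal) | 50 | 12.5 | 15 |
| 8 (high) | 80 | 20 | 24 |

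The multiple is 10 × 0.25 = 2.5. The ratio to target is 2.5/3 = 0.833, a shortfall of 16.7%; log10(0.833) = −0.079.

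**Step 3. Try other readings.**

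- 0.3 mL: 10 × 0.1/0.3 = 3.33 times routine, or 6.7–26.7 × 10^5.
- All three 0.1 mL portions given to one person: 10 × 0.3/0.4 = 7.5 times, or 15–60 × 10^5. This contradicts the single injection.
- Exactly three times routine in 0.1 mL requires 10 × 0.1/3 = 0.333 mL. Only this volume reproduces 6–24 × 10^5.

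**Step 4. Check the aliquot plan.** Three injections and one full check dose, each at three times routine, need 4 × 3 = 12 routine doses. The vial holds 10, so the four-portion plan and the stated multiple cannot both stand.

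**Step 5. When would a range check detect it?** The injected dose falls below 6 × 10^5 only if 2.5x < 6, where x is CFU per routine dose in units of 10^5; that is, x < 2.4. Any vial between 2.4 and 8 × 10^5 per routine dose yields 6–20 × 10^5, inside the specified range although given at 2.5 times routine.

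**Step 6. Volumes that give three times routine.**

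- 0.333 mL with 0.1 mL injected: 50 × 0.1/0.333 = 15 × 10^5. After three injections 0.333 − 0.300 = 0.033 mL remains, one routine dose (2–8 × 10^5). After two injections and a full 0.1 mL check aliquot the same 0.033 mL remains as slack.
- 0.4 mL with 0.12 mL injected: 50 × 0.12/0.4 = 15 × 10^5. After three injections 0.4 − 0.36 = 0.04 mL remains, also one routine dose.

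Dead volume is ignored throughout.

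**The case against.** The strongest reply is that the volume is explicitly provisional and secondary to the dose. The protocol fixes the CFU range, promises a laboratory check before the study, keeps an aliquot to verify each preparation, and reviews concentrations after Phase A. On its own nominal figure the injection holds 12.5 × 10^5 CFU, which meets the written range. The shortfall of 0.08 log10 is small beside a fourfold label range, and it applies to every participant in a study without randomised arms, so it biases no between-arm comparison. Only the bottom fifteenth of the label range's width, (2.4 − 2)/(8 − 2), gives a dose below the minimum. The preparation SOP is not shown and may test more than the range. Finally, a 0.03–0.04 mL check aliquot may be lost to dead volume, so 0.4 mL may have been a practical choice.

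Much of this stands. The effect is small, nothing in the protocol shows that 2.5 times routine would fail, and whether the laboratory check would catch the discrepancy is unknown. None of it reconciles the figures. The only numerical target in print is a fourfold range, which is a blunt test for a 1.2-fold discrepancy. The per-vial check is post hoc; if it is done by plate count, as for the vaccine vials under Confirmation and quantification of mycobacterial recovery, results take four weeks. The Phase A review can change only Phase B. The dead-volume point is fair against the small check aliquots, but not against two injections plus a full check aliquot, or against restating the dose.

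**Conclusion.** The concern holds. As written, the preparation delivers 5–20 × 10^5 CFU (nominally 12.5 × 10^5, 2.5 times routine) where the protocol specifies 6–24 × 10^5 (nominally 15 × 10^5, 3 times routine). It is 16.7% low, and the four-portion plan is impossible at the stated multiple. This assumes one vial per 0.4 mL, label content as printed, one 0.1 mL injection per participant and no losses on drawing up. The direction is towards a lower dose, so it adds no safety concern. It is an inconsistency in the planned preparation, not evidence that participants will be under-dosed, since the volume may yet change. It should still be corrected before the first injection, because the dose is justified only at three times routine.

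**What to change.** Choose one of two routes and make the Study design and Administration text agree.

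1. **Keep three times routine (preferred, because this is the dose the protocol justifies).** Reconstitute in about 0.33 mL and inject 0.1 mL. Taking two injections and a full 0.1 mL check aliquot from each vial avoids the dead-volume problem. Three injections with a check aliquot of about 0.03 mL, or 0.12 mL injections from 0.4 mL with a 0.04 mL check, are possible if the laboratory confirms that the small aliquot can be recovered and counted.
2. **Keep 0.4 mL and 0.1 mL.** Restate the dose for both phases as 5–20 × 10^5 CFU, 2.5 times routine, and acknowledge that this is below the multiple used in the cited work.

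Under either route, state that the pre-study laboratory check compares the prepared dose with a routine dose from the same product (expected ratio 3.0 or 2.5), as well as with the CFU range.

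The cost is wording in the protocol and the preparation SOP; no visits, samples or participants are added. Two injections per vial instead of three uses somewhat more vaccine: if sessions are always full, 10/2 = 5 vials instead of 4 (10/3 rounded up) in Phase A, and 20/2 = 10 instead of 7 (20/3 rounded up) in Phase B. According to Study status, recruitment had not begun when the article was submitted.
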